6.1. Demographic measurements

Parameters for describing proband characteristics in this study are:

- Body weight [kg], body height [cm], BMI [kg/m^2^]

- Sex [male/female]

- Age [year]

- Medical history

- Medication use

- eating habits/diet restraints (vegan, vegetarian,…)

- ethnicity

- smokers/ non-smokers

- level of regular physical training

6.2. Parameters for assessing protocol compliance

Parameters for assessing protocol compliance in this study are (checked by study nurse):

- Refrain from substances that might alter gut microbiota (including proton pump inhibitors, laxatives and antibiotics) unless medically necessary

- Collection of the required samples (3 fecal samples, 3 urine samples)

- Completion of measurement of hydrogen content of exhaled air after lactulose intake (lactulose breath test).

1. SAFETY of conducted procedures
   1. Fecal and urine sample collection

Volunteers will be provided with individually numbered cryotubes and will be asked to collect fecal and urine samples using the restrooms at the Institute of Microbiology, ETH Zurich. After sample collection, the proband snap-freezes the samples in liquid nitrogen and transfers the samples to a -80°C freezer (Biosafety Level 2). Liquid nitrogen and -80° freezers can be handled very safely with some basic training and compliance with few basic precautions. During recruitment we will ensure that all probands are trained in handling liquid nitrogen and 80°C freezers at biosafety level 2 (this is the case for near all scientific members at ETH). All probands will wear suitable protection (gloves and googles). As handling liquid nitrogen is part of their regular working routine, this step will not impose an additional risk to our volunteers. Furthermore, handling of stool or urine from other individual carries a small risk for infections. However, this is not the case if an individual handles his or her own stool or urine and autoinfection is not a concern.

7.2. Lactulose breath test

The lactulose breath test is a non-invasive, routine diagnostic test. Breath samples are obtained with hand-held breath test devices before and after intake of 50 g lactulose/sucrose. Exhaled hydrogen concentrations can be measured in parts per million (ppm). The technology is perfectly safe. Minor adverse events include diarrhea, bloating and mild abdominal pain. Sever adverse events in healthy individuals are unknown.

- 1. Procedures for discontinuation

If a subject discontinues participation one of the investigators will immediately be called. If a subject is withdrawn, the subject will have contact to the principal investigator (if possible) or one of the additional investigators. Adverse events will be followed up. Data of these subjects will be analyzed as censored at the time of withdrawal. If no analysis of the microbial composition/metabolites within the samples is possible due to limited data over time, measurements will be regarded as a drop out.

1. STATISTICS AND DATA ANALYSIS
   1. Analysis of fecal and urine samples

**Microbial composition:**

- Microbial DNA will be extracted from fecal samples and analysed as described previously [10] by member of the [name] lab, Institute of Microbiology, ETH Zurich. 16S rRNA sequencing will be performed in collaboration with the Functional Genomics Center Zurich and sequencing reads will be evaluated according to established protocols [10] by the [name] lab, Swiss Institute of Bioinformatics, University of Zurich by HPC-CLUST. Additional genetic, microbiological or immunological analyses are also possible.

**Metabolite composition:**

- Monitoring compositional metabolic changes requires the identification and quantification of large portions of metabolites that constitutes these metabolomes. Such global profiling of samples can be achieved by untargeted metabolomics on the basis of mass spectrometry [21]. After metabolite extraction ([name] lab), samples will be analysed by the [name] lab, Institute of Molecular Systems Biology, ETH Zurich. Additional metabolic analyses are also possible.
  1. Lactulose breath test

The lactulose breath test will be evaluated according the standard procedures using established algorithms. Hydrogen concentrations on both groups (lactulose vs. sucrose intake) will be compared using the Mann-Whitney U test.

- 1. Significance level

Significance levels will be determined as described in [12].

- 1. Dropouts

Dropouts will be replaced until 40 (20 for each group) complete sets of samples including the results for the lactulose breath test are available.

1. Study related regulatory issues
   1. Recruitment and Informed Consent

Prior to study enrolment, written informed consent must be obtained from each subject. It is the responsibility of the investigator to obtain this written informed consent after adequate explanation to the subject of the aims, methods, source of funding, the anticipated benefits and potential risks of the study and the discomfort it may entail. Written informed consent should be obtained prior to screening, with the understanding that consent may be withdrawn at any time without prejudice. Two copies of the informed consent are signed: one is given to the subject and one is retained in the Investigator Site File on site.

The right of the participant to refuse to participate without giving reasons must be respected. All participants are free to withdraw at any time from the protocol without giving reasons and without prejudicing possible future treatments at our facility. There is no state of dependence between the proband and the investigators.

- 1. Confidentiality

The Principal Investigator will preserve the confidentiality of participants taking part in the study and is registered under the Data Protection Act.

- 1. Funding

Prof. [name], Institute of Microbiology, ETH Zurich and "Klinik für Gastroenterologie and Hepatologie", Universitätspital Zürich, are funding this study.

- 1. Participant compensation

For completing this study subjects will receive a compensation of 200.- CHF for the discomfort they may experience while participating in the trial (mainly loss of time, collection of fecal samples might cause discomfort, lactulose breath test). For completing only a part of the study, no compensation will be granted. Volunteers will be reimbursed after handing over the last set of samples (14 day after the lactulose breath test).

- 1. Preventive measures

Participants will be asked about their experience in handling liquid nitrogen and -80°C freezer at biosafety level 2. If they feel uncomfortable in snap-freezing their samples or storing them in a -80°C freezer, they will be excluded.

1. Duties of the principle investigator

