1. STUDY SYNOPSIS

| Study Title: | Elucidating the influence of lactulose intake on the gut microbiota composition. |
| --- | --- |
| Protocol Version and Date: | Protocol ID: KEK-ZH-Nr.  Version: 1.0  Date: 16.6.2014 |
| Methodology: | This is a clinical study for investigating the influence of lactulose (as used for the lactulose breath test) on the composition and metabolic activities of the intestinal microbiota. Healthy volunteers will donate fecal samples and urine before (24 h) and after (1-2d, 14d) a routine lactulose breath test. Samples will be analyzed for their microbiota composition and key metabolites. |
| Study Duration: | Data acquisition for the study will be performed from October 2014 to March 2016. Total study duration for each participant is 4 hours maximum (including preparation time) at the study center for the breath test plus collection of fecal samples and urine. |
| Study Center: | Division of Gastroenterology and Hepatology  University of Zurich  [name]  [name] |
| Objective(s): | Primary objective:   - Influence of lactulose intake on gut microbiota composition   Secondary objectives:   - Influence of lactulose intake on metabolic profiles within the fecal ecosystem and the host (urine) |
| Number of Subjects: | 40 healthy volunteers |
| Diagnosis and Main Inclusion Criteria: | - Subjects free of abdominal complaints (=healthy). - Written informed consent - Working at ETH Zurich/University of Zurich, experience in handling of liquid nitrogen on biosafety level 2 |
| Main Exclusion Criteria: | - Age under 18 - Previous history of gastrointestinal disease or surgery (excludes appendectomy, hernia repair and anorectal disorders) - Known diabetes mellitus, scleroderma, neurological impairment or other major current disease - Subjects unable to stop medication that alters gut flora: proton pump inhibitors, laxatives and antibiotics at least 4 weeks before study entry. - Pregnancy beyond week 12 (no pregnancy test will be performed) - Involvement in any other clinical trial during the course of this trial, nor within a period of 14 days prior to its beginning or 14 days after its completion |
| Study Schedule: | October 2014 – March 2016: Recruitment, data collection and analysis. |

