Before the study, there will be one study visit to inform the probands and to obtain informed consent and address basic medical history and gastrointestinal complaints. This is done by one of the MDs in a seminar room at the Institute of Microbiology, ETH Zürich. Specifically, probands will be asked about loss of appetite, nausea, early satiety, sense of abdominal fullness, vomiting, abdominal pain, dysphagia, heartburn, reflux, sweating/ shivering after meals and diarrhea. In addition, probands will be asked about their current medication (proton pump inhibitors, antibiotic therapy, laxative drugs within the last four weeks) previous abdominal surgery, additional chronic diseases, pregnancy, and current or past (≤2 weeks) participation in addition clinical trials (questionnaire Appendix), eating habits (vegetarian, vegan), ethnicity, smokers/non-smokers, the amount of regular physical exercise, stool frequency/consistency (Bristol Stool Scale), weight and height.

The study will be finished within approximately 16 days for each individual. The study includes one examination of approximately 4 hours, the remaining parts of the studies (collection of feces and urine and proper storage of these samples) will be done at the working place of the proband (ETH Hoenggerberg, Zurich).

The anticipated study duration for is from October 2014 to March 2016. Total study duration for each participant is 4 hours maximum (including preparation time) at the study center for the breath test plus collection of fecal samples and urine.

- 1. Method of Randomization and Blinding

To randomly assign our probands to lactulose/sucrose groups, we will apply a sealed envelope technique. Lactulose and sucrose (supermarket) will be filled in tubes labeled with numbers indicated within the envelope. That way, neither the proband nor the study nurse/PI will know the group assignment. Randomization will be ensured using the following program:

<http://www.graphpad.com/quickcalcs/randomize1.cfm>

- 1. Method of encryption

To ensure encryption of samples , cryotubes with fecal and urine samples will be pre-labeled with the study number and the respective date respectively to the breath test. The key for encryption will be stored at University Hospital Zurich. Therefore, only the principal medical investigator, but not the microbiologists will be able to decode the study number and assign this identifier to an individual.

- 1. Unblinding Procedures (Code break)

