An Emergency Code Break will be available to the investigator. This Code Break should be opened only in emergency situations when the identity of the investigational intervention must be known by the investigator in order to provide appropriate medical treatment.

1. Recruitment / Participant Entry / Discontinuation
   1. Pre Registration Evaluations

Volunteers will be recruited via public advertisement on notice boards at ETH Hoenggerberg Zurich, as well as by an Email to all members of the Institute of Microbiology and other departments at ETH Hoenggerberg. Exemplary advertisements/Email for potential volunteers are shown in the appendices. Potential volunteers can contact [name], who will give a short summary of the aim and benefits of the study and will check whether the potential volunteers can be included in the study (inclusion criteria/exclusion criteria). No individual-related data will be registered during this telephone interview. (See document 4b-Rekrutierung_Telefonfragebogen).

Interested subject will receive study information by email. Medical history and current treatment will be extracted through a standardized interview before the study after informed consent has been obtained. This is done by one of the MDs in a seminar room at the Institute of Microbiology, ETH Zürich.

- 1. Inclusion criteria

• Subjects free of abdominal complaints or symptoms

• Written informed consent

• Working at ETH Zurich/University of Zurich and trained and experienced in handling liquid nitrogen/-80°C freezers at biosafety level 2.

• Age: 18 to 85 years

- 1. Exclusion criteria
- Previous history of gastrointestinal disease or surgery (excludes appendectomy, hernia repair and anorectal disorders)
- Known diabetes mellitus, scleroderma, neurological impairment or other major current disease
- Subjects with antibiotic therapy, proton pump inhibitors or laxatives within the last four weeks.
- Pregnancy beyond week 12. The lactulose breath test is safe also during pregnancy; however, pregnancy might alter the human microbiota and there is a slight risk that advanced pregnancy would be a confounder in our study. No pregnancy test will be performed.
- Involvement in any other clinical trial as proband during the course of this trial or within a period of 14 days prior to its beginning
  1. Criteria for discontinuation

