Subjects may be discontinued from study treatment and assessments at any time, at the discretion of the Principle Investigators. Specific reasons for discontinuing a subject from this study are:

• Withdrawal of informed consent

• Protocol non-compliance (protocol deviation)

- - 1. Voluntary discontinuation by a subject

Subjects are free to discontinue their participation in the study at any time. Subjects who discontinue from the study should always be asked about the reason(s) for their discontinuation and about the presence of any adverse events. Adverse events should be followed up. Data of these probands will be analyzed. However, data of probands will be anonymized and all contact data and identifying information will be deleted from the subject identification log..

1. Efficacy variables

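### Section 8.4 recruits until each arm has 20 complete sample sets, without saying who may know a dropout's arm or whether partial sets are analysed, and does not fit the protocol's other withdrawal rules

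*Protocol*

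**What the plan says.** Four parts of the protocol bear on this.

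- **Target and replacement.** Section 8.4: "Dropouts will be replaced until 40 (20 for each group) complete sets of samples including the results for the lactulose breath test are available". By Section 6.2, the required samples are three fecal and three urine samples, and the breath test must also be completed. The synopsis gives the number of subjects as "40 healthy volunteers" and does not say whether these are participants randomised or complete sets.
- **Voluntary discontinuation.** Section 5.4.1: "Data of these probands will be analyzed", with no exception.
- **Discontinuation procedures (end of Section 7).** "Data of these subjects will be analyzed as censored at the time of withdrawal". Where composition or metabolites cannot be analysed "due to limited data over time, measurements will be regarded as a drop out". This is the only definition of a dropout in the protocol.
- **Blinding.** Drinks are in numbered tubes and allocation is by sealed envelope: "That way, neither the proband nor the study nurse/PI will know the group assignment". On unblinding: "This Code Break should be opened only in emergency situations". No section names an unblinded role or says how replacements are allocated.

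**The concern.** A recruitment target met by completeness within each arm is fixed by what happens after randomisation. That raises three problems.

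First, topping up each arm separately needs the allocation of every dropout, and no described role has it. If the gap is filled informally, the blind is at risk.

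Second, the fate of a participant with some usable samples is undefined, and so is the final analysed number.

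Third, if replaced participants drop out of the analysis, the arms are compared on completers. Randomisation protects that comparison only if completeness is unrelated to the drink, or related to it in a way that does not matter for the outcome. The protocol gives reason for doubt. The stool sample after the drink is due within two days, at the workplace and during working hours. Section 3.1 notes that lactulose is used to treat constipation, and the adverse events listed for the test are diarrhoea, bloating and abdominal pain. All of these concern bowel function, in a trial whose primary objective is gut microbiota composition.

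**Working it through.** **1. The stated figure.** 20 + 20 = 40, so Section 8.4 is internally consistent. The protocol gives no effect size, SD, power or dropout rate, so 40 cannot be re-derived as a sample size.

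**2. The rules side by side.** Take a participant who gives the baseline and the 1-2 day samples and then withdraws before day 14.

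- Section 5.4.1: the data are analysed.
- Discontinuation procedures: the data are analysed up to withdrawal, and the person is not a dropout as long as analysis is possible.
- Section 8.4: the set is incomplete, so it does not count towards the 20 and recruitment must continue.

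All three can be followed together only if extra volunteers are added while this person stays in. The analysed number is then 40 + w, where w is the number withdrawn with usable data: 42, 44 or 48 for w = 2, 4 or 8 (assumed counts). If the person is substituted, it is 40. The protocol does not say which. The term 'censored' does not help, because it belongs to time-to-event data and has no evident meaning for samples at three planned times.

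**3. Can 20 per group be reached without knowing the arm?** Assume 40 randomised 20:20, k dropouts falling at random, and k replacements allocated 1:1 without knowledge of the dropout's arm, all of whom complete. The chance of ending at exactly 20:20 is the sum over x of P(x of the k dropouts are lactulose; hypergeometric) × P(x of the k replacements are lactulose; binomial with probability 0.5). For k = 2 this is 0.244 × 0.25 + 0.513 × 0.5 + 0.244 × 0.25 = 0.378.

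| Dropouts k | Chance of 20:20 |
|---|---|
| 1 | 50% |
| 2 | 38% |
| 4 | 28% |
| 8 | 21% |

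The rule can be met reliably only if someone, or a pre-coded list, holds each dropout's arm.

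**4. Size of the bias if only completers are compared.** Every input here is an assumption, including a single-number endpoint in SD units.

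*(a) General form.* If a fraction d of an arm drops out, and dropouts differ from completers by a gap of g SD, the completer mean differs from the mean of all randomised by d × g. The spurious difference between arms is (d1 − d2) × g, and the expected number randomised per arm is 20/(1 − d).

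| Dropout, arm 1 / arm 2 | Expected total randomised | Shift for g = 0.5 to 1 SD |
|---|---|---|
| 5% / 5% | 21.1 + 21.1 = 42 | 0 |
| 10% / 5% | 22.2 + 21.1 = 43 | 0.025 to 0.05 SD |
| 20% / 5% | 25.0 + 21.1 = 46 | 0.075 to 0.15 SD |
| 30% / 10% | 28.6 + 22.2 = 51 | 0.10 to 0.20 SD |

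*(b) A deliberately severe form.* Suppose the slowest fraction q of one arm, by bowel transit, fails the sampling window and is replaced, with no loss in the other arm. Suppose transit correlates r with the endpoint. The mean shift in transit is φ(z)/(1 − q), with z the upper-q normal quantile: 0.195, 0.350 and 0.497 for q = 0.1, 0.2 and 0.3. Multiply by r for the bias. Divide by SE = √(2/20) = 0.316 for the noncentrality of a t test with 38 df, at an assumed two-sided 5% level.

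| q | r | Bias | Actual type I error |
|---|---|---|---|
| 0.1 | 0.5 | 0.10 SD | 6.0% |
| 0.2 | 0.5 | 0.18 SD | 8.4% |
| 0.3 | 0.5 | 0.25 SD | 11.9% |
| 0.3 | 0.7 | 0.35 SD | 18.8% |

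**5. Scale.** With 20 per arm, the difference detectable at an assumed two-sided 5% level and 80% power is (1.960 + 0.842) × 0.316 = 0.89 SD.

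**The case against.** The best defence is that Section 8.4 says when recruitment stops, not who is analysed. It nowhere excludes partial sets, and the two sections that do speak of analysis point towards keeping them. Analysis populations may also be set out in an SAP that is not shown. This stands in part: a completers-only analysis is an inference, not the text. But the protocol speaks of replacing people, and its headline number equals the number of complete sets, so the inference is the natural one. An SAP also cannot repair, after the event, how replacements were allocated.

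Several stronger readings are tempting, and the documents do not support them.

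- *That dropout will fall mainly in one arm.* No rates are given. Participants are free of abdominal complaints, must already have managed a workplace sample before the drink, take a single drink, are followed for about two weeks and are paid only on completion. The listed adverse events are called minor. Slow transit on sucrose and diarrhoea on lactulose could even offset each other. The severe form in step 4(b) assumes loss in one arm only and a correlation with change in composition that nothing in the protocol supplies.
- *That the rule forces unblinding.* A holder of the tube code could supply replacements without telling the nurse or PI. The defect is that no such role or procedure is stated.
- *That the three withdrawal rules flatly contradict one another.* Two concern the use of data and one concerns enrolment. They are unreconciled, chiefly in what a dropout is.
- *That a protocol deviation removes data.* Section 5.4 lets the investigators discontinue such a subject from treatment and assessments. It does not say that data already collected are discarded.
- *That only the baseline and 1-2 day samples matter for the primary comparison.* The protocol names no primary time point.

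**Conclusion.** The point holds as a defect in how the protocol fixes replacement. Three things rest on the text alone: the target depends on completeness after randomisation within each arm; meeting it needs allocation knowledge that no described role has; and the meaning of dropout differs between Section 8.4 and the discontinuation procedures, so that the treatment of partial sets and the analysed number (40 or more) are open.

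Bias in the comparison is a risk of unknown size, not a demonstrated consequence. It requires that replaced participants be left out, that dropout differ by arm, and that dropouts differ from completers on the endpoint. Under the assumed inputs it runs from about 0.03 SD to 0.35 SD. It is nil if dropout is equal in the two arms and dropouts differ from completers alike in both. At the upper end it is not negligible against a detectable difference of about 0.89 SD; at the lower end it is. The change is worth making because it protects the randomised comparison and the blind at very little cost.

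**What to change.** In Section 8.4, state that:

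- every randomised participant who took the drink and has usable samples is analysed in the assigned arm;
- extra volunteers are added to such participants and do not substitute for them;
- extra volunteers receive the next unused envelope regardless of arm, with the recruitment stop expressed as a total that can be counted blind; or, if 20 per group is to be kept, a named independent code-holder assigns them.

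Use one definition of dropout in Section 5.4.1, the discontinuation procedures and Section 8.4. In the discontinuation procedures, replace the reference to censoring with a statement that all samples given up to withdrawal are used. Say in the synopsis whether 40 counts participants randomised or complete sets. The model for partial sets can be left to the SAP.

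The cost is a few sentences. Arms may end slightly unequal and some sets incomplete. Imbalance itself costs almost nothing: at 19 and 21 the standard error is √(1/19 + 1/21) = 0.317 SD, against 0.316 SD at 20 and 20.
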